# Investigating the efficacy of an individualized metacognitive therapy program (MCT+) for psychosis: study protocol of a multi-center randomized controlled trial

**DOI:** 10.1186/s12888-016-0756-2

**Published:** 2016-02-27

**Keywords:** Schizophrenia, Metacognitive training, Psychosis, Cognitive biases, Delusions

## Abstract

**Background:**

Psychological interventions are increasingly recommended as adjunctive treatments for psychosis, but their implementation in clinical practice is still insufficient. The individualized metacognitive therapy program (MCT+; www.uke.de/mct_plus) represents a low-threshold psychotherapeutic approach that synthesizes group metacognitive training (MCT) and cognitive behavioral therapy for psychosis, and addresses specific cognitive biases that are involved in the onset and maintenance of psychosis. It aims to “plant the seed of doubt” regarding rigid delusional convictions and to encourage patients to critically reflect, extend and change their approach to problem solving. Its second edition also puts more emphasis on affective symptoms. A recent meta-analysis of metacognitive interventions (MCT, MCT+) indicate small to moderate effects on positive symptoms and delusions, as well as high rates of acceptance. Nonetheless, no long-term studies of MCT+ involving large samples have been conducted.

**Methods:**

The goal of the present multi-center, observer-blind, parallel-group, randomized controlled trial is to compare the efficacy of MCT+ against an active control (cognitive remediation; MyBrainTraining^©^) in 328 patients with psychosis at three time points (baseline, immediately after intervention [6 weeks] and 6 months later). The primary outcome is change in psychosis symptoms over the 6-month follow-up period as assessed by the delusion subscale of the Psychotic Symptom Rating Scale. Secondary outcomes include jumping to conclusions, other positive symptoms of schizophrenia, depressive symptoms, self-esteem, quality of life, and cognitive insight. The study also seeks to elucidate mediating factors that promote versus impede symptom improvement across time.

**Discussion:**

This is the first multi-center randomized controlled trial to test the efficacy of individualized MCT+ in a large sample of patients with psychosis. The rationale for the trial, the design, and the strengths and limitations of the study are discussed.

**Trial Registration:**

The trial is registered through the German Clinical Trials Register (www.drks.de) as DRKS00008001. Registered 6 May 2015.

## Background

Schizophrenia remains a stigmatizing and chronic disorder that affects approximately 1 % of the population worldwide and is among the world’s top ten causes of chronic disability [1]. Due to the poor quality of life among many of those affected [2] and the large healthcare costs incurred through repeated hospitalizations [3], improved treatment for schizophrenia is needed. Although antipsychotic medications remain the treatment of choice for schizophrenia, up to 60 % of patients do not respond to antipsychotic medications [3] and rates of non-adherence are as high as 60 % within the first year of treatment [4]. Furthermore, among those who are compliant with medications, a minority (approximately 40 %) have a good symptomatic outcome and recovery rates are only around 20 %. Moderate effect sizes have been reported for improvement in positive symptoms relative to placebo; however, non-pharmacological approaches are also necessary to treat cognitive symptoms, such as cognitive biases [5–7].

The current study is designed to test the effectiveness of an innovative treatment for psychosis, the individualized metacognitive therapy program (MCT+), compared to an active control group, which completes cognitive remediation. The group version of the treatment program, metacognitive training (MCT) was developed by [name] and colleagues in 2002/2003 and adopts a metacognitive perspective (i.e., “thinking about one’s thinking”). The MCT approach is based on significant evidence from many research groups [19–25], including our own [26–29], that cognitive biases underlie the formation and maintenance of schizophrenia. While patients are often unaware of these cognitive biases (such as overconfidence, incorrigibility and hasty decision-making), they are not limited only to delusional beliefs, but can also be observed in daily delusion-neutral situations. As discussed in recent publications [30, 31], MCT aims to “plant the seed of doubt” regarding delusions through corrective (“aha!”) experiences in an entertaining, playful and collaborative manner. In this way, MCT aims to raise patients’ awareness regarding the negative impact of cognitive biases, which contribute to the pathogenesis and perpetuation of positive symptoms.

The intervention borrows from CBTp, CR and psychoeducational approaches by focusing on symptoms, presenting multiple cognitive exercises and providing general information on the disorder. However, differing from CBTp, MCT adopts a “backdoor” approach in which general cognitive processes are first addressed before examining how these biases may lead to problems in everyday life and psychotic symptoms, respectively. Additionally, rather than focusing on accuracy and traditional neuropsychological faculties (e.g., memory, attention) as in CR, MCT particularly attempts to attenuate participants’ overconfidence in errors (e.g., by asking patients to consider their level of certainty before making a final decision) and delay decision-making for momentous judgments. Therefore, the goal of MCT is not to dissuade patients from their delusional thoughts, but to promote doubt regarding the likelihood that the delusional thought content accurately reflects reality.

The individualized version of MCT, termed MCT+, was recently developed to allow for more detailed targeting of patient-specific problems, which cannot be addressed in group therapy [32, 33]. Importantly, overcoming the above-mentioned barriers to psychotherapy, MCT+ is short (up to 12 sessions), but has an evidence-based mechanism of action, and although it is highly structured and fully manualized, the therapist can select the therapy units that fit best to the patient’s current difficulties and cognitive biases. Based on patient feedback and research findings that patients wish to prioritize treatment of affective symptoms, in the newest edition, more focus has been placed on affective symptoms. Like the group variant, in MCT+ therapists first teach participants about cognitive biases and dysfunctional emotional regulation before individual problems are addressed. To increase the dissemination and use of MCT and MCT+; materials are available for free in many world languages. The group MCT is available in 33 language versions and MCT+ is currently available in 10 versions.

As summarized in a comprehensive review [30], the feasibility, safety and efficacy of group MCT has been demonstrated in several study trials. The intervention is well-accepted by patients, who indicate that they find the training to be fun and would recommend MCT to others [30, 34, 35]. A recent meta-analysis [35] revealed that MCT yields significant small to moderate effects on positive symptoms (*g* = .34) and delusions (*g* = .41) in comparison to control conditions and that effects are higher for the three completed trials of individualized MCT (positive symptoms: *g* = −0.53; delusions: *g* = −0.26). However, it is important to point out that two of the studies included in these analyses utilized the materials for group MCT in an individualized setting [36–38]. Therefore, there has been only one trial of MCT+ [34], which yielded small to moderate significant improvements (η_partial_^*2*^ = .10) in delusions and positive symptoms compared to an active control group. Despite the overall positive effects, notably, one large trial by van Oosterhout and colleagues (2014) found no superiority for group MCT compared to a treatment-as-usual (TAU) control group for symptoms. Although the reasons for this “outlier” remain unclear, the study included patients with moderate to severe delusions and used an older version of group MCT, which did not highlight the role of (over) confidence. While the training is aimed at improving positive symptoms, clinical experience indicates that patients with acute symptoms often have difficulty engaging in the group setting and have limited ability to acknowledge cognitive biases. Therefore, it is now recommended that trainers screen out such patients for the group intervention. Such patients may be more amenable to MCT+ as the individualized setting is more flexible and allows more time for addressing such acute symptoms. Additionally, the earlier version of MCT did not include as much focus on attenuating confidence in the face of incomplete or ambiguous evidence, which is now a core component of the training. Despite the possible explanations for these null findings, it must also be considered that MCT is not helpful for all patients [39].

While some studies have demonstrated significant improvements in cognitive biases (especially jumping to conclusions or data gathering) thought to be implicated in delusional ideation [40–45], others have not been able to find significant differences [36, 46, 47] in comparison to active control and wait-list groups. Recent studies revealed significant improvements in cognitive insight for MCT compared to an active control group [48] and a wait-list control group [46]; however, no significant differences were reported in the van Oosterhout et al. trial. One trial found a significant group difference for improvement in social functioning [49]; however, in this study, MCT was combined with social cognition training.

Despite these promising findings, the long-term effects of MCT and particularly MCT+ remain largely unknown. In one recent MCT trial, improvement on the PSYRATS was sustained for up to three years, and “sleeper effects” for self-esteem and global quality of life emerged only at the three year follow-up [47]. Nonetheless, there has only been one trial of MCT+, which was small (*n* = 48) and did not involve follow-up assessment. Moreover, MCT+ has been updated since this study and now includes more focus on affective symptoms and stigma. A large trial is also needed to elucidate for which symptom domain MCT+ is the most helpful and symptoms or demographic constellations (e.g., age, gender, education) that may moderate outcome.

### Aims of the trial

The primary aim of this study is to investigate the effectiveness of MCT+ versus computerized cognitive remediation (CR; MyBrainTraining^©^) in individuals with psychosis.

The primary research question is:Does MCT+ result in a greater reduction in rater-observed symptoms of delusions, as measured by the Psychotic Symptom Rating Scales (PSYRATS delusions subscale), compared to computerized CR at the end of treatment (6 weeks)?

Secondary research questions are:2)Does MCT+ result in a greater reduction in other positive, negative and affective psychopathology than computerized CR as measured by the Positive and Negative Symptoms Scales (PANSS)?3)Does MCT+ result in a greater reduction in jumping to conclusions than computerized CR? Is change in jumping to conclusions associated with improvement in positive symptoms?4)Does MCT+ result in a greater reduction in self-reported symptoms of depression and/or a greater increase in quality of life, self-esteem, and cognitive insight than computerized CR?5)Does computerized CR result in a greater improvement in neuropsychological functioning than MCT+?6)Are baseline characteristics or therapy motivation predictive of treatment response to MCT+?

Although small, yet significant, decreases in psychosis symptoms have been reported in some studies of CR interventions [13], based on previous work, we hypothesize that MCT+ will lead to a greater decrease in delusions as compared to patients in the computerized CR group at post and follow-up test sessions (Q1). Cognitive remediation is deemed an appropriate comparison group for the present study since its feasibility has been asserted, and because it offers some amelioration of neuropsychological symptoms, but does not address cognitive biases at the core of MCT+. We further hypothesize that, compared to the control group, we will find a greater reduction in the PANSS positive syndrome [50] at the same time points for MCT+ participants (Q2). Given previous mixed results regarding improvement in jumping to conclusions [30, 51], we hypothesize that data gathering will improve in both groups, but that only improvement in the MCT+ group will be significantly associated with improvement in delusions (Q3). Because the newest version of MCT+ places more focus on affective symptoms and significant (sleeper) effects have already been detected for quality of life and self-esteem in group MCT (which did not include these new therapy units), we anticipate that participants who complete MCT+ will demonstrate improvements in depressive symptoms, quality of life and self-esteem, which are superior to the control group (Q4). As mentioned above, a limited number of previous studies have yielded mixed findings regarding the effects on cognitive insight. Therefore, we do not expect changes in this domain. Trials on CR programs, as well as our own work, suggest that CR exerts a small to moderate effect on neurocognition [47, 52]. Therefore, it is expected that participants in the control group will experience greater improvements in neuropsychological functioning than those in MCT+ (Q5). Finally, we posit that participants with greater therapy motivation will have a better response (i.e., greater decrease in delusions) to MCT+ (Q6). Based on previous MCT trials [53], we hypothesize that participants with symptoms in the moderate range will benefit most from MCT+.

## Methods/Designs

### Study design

The design of the study is a multi-center, assessor-blind, parallel group, randomized controlled trial. Patients will be randomized to MCT+ or computerized CR. The study protocol has been approved by the German Psychological Society (*Deutsche Gesellschaft für Psychologie*; SM_102015_amds_div), as well as by local ethics committees (Medical Faculty of the Ruhr-University Bochum; Medical Faculty Mannheim of the University of Heidelberg and University Hospital Mannheim). It has been registered at the German Registry for Clinical Studies under the number DRKS00008001.

### Participants

The study population will consist of individuals with psychosis (as confirmed by the Mini International Neuropsychiatric Interview, 5th Ed [M.I.N.I.]) [54]. Diagnoses according to the *Diagnostic and Statistical Manual of Mental Disorders – 5th edition* (DSM-5) [55] are then derived from information gained from the M.I.N.I. To enhance recruitment and generalizability, the study is being conducted in four different German clinics for patients with psychosis: the Department of Psychiatry and Psychotherapy at the University Medical Center Hamburg-Eppendorf, the Department of Psychiatry and Psychotherapy at the Central Institute of Mental Health in Mannheim, the Clinic for Psychiatry, Psychotherapy and Preventative Medicine at the LWL University Hospital Bochum, and the Clinic for Psychiatry and Psychotherapy at the Asklepios Clinic North in Hamburg-Wandsbek. Each center has specialized out- and inpatient clinics for treatment of psychosis.

### Eligibility criteria

Generalizability of study results is of main importance; therefore, eligibility criteria were chosen to recruit a broad sample representative of the population of patients with psychosis. Participants between the ages of 18 and 65 who meet the following criteria will be included in the study: a) primary diagnosis of psychosis as verified by the M.I.N.I. and supplemented by diagnostic criteria for schizophrenia and schizoaffective disorder from the DSM-5; b) provide informed consent; c) sufficient understanding of the German language. Exclusion criteria include: a) IQ < 70 (according to a premorbid intelligence vocabulary test); b) PANSS scores ≥ 5 for hostility and non-cooperativeness (G8, P7); c) endorsement of suicidal intent; d) current alcohol or substance dependence (abstinence must be > 6 months), excluding tobacco; e) any form of documented or suspected major neurological or general medical condition that might be responsible for the psychotic manifestations; f) participation in MCT+ within the past 12 months.

### Procedure and treatment allocation

Recruitment occurs in different ways: recruitment by study staff during inpatient stays, referrals from mental health professionals at clinics both within the cooperating centers and in the community (including private practices), and by self-selection through advertisements or word-of-mouth, for example, from Internet searches for schizophrenia treatment in the community. Interested patients receive an informational leaflet and undergo a screening interview by telephone or in-person with research assistants to assess eligibility. If patients appear eligible upon initial contact, they are invited for baseline testing in which informed consent is obtained (or it is obtained before testing for patients with guardians for medical decision-making).

Blinded in-person assessments conducted by trained study research assistants, psychologists or psychiatrists are performed at baseline, 6 weeks and 6 months after baseline (see Table 1). All raters complete a rater-training workshop and also receive individual training in which they are observed as the measures are administered. The 6-week intervention phase begins directly after completion of baseline testing. To diagnose or confirm the diagnosis of psychosis or an affective disorder with psychotic features, as well as to rule-out acute suicidality and substance dependence, a semi-structured interview with the M.I.N.I. is completed with all patients at baseline and 6-month sessions. A questionnaire for intervention group preference and motivation is completed at the beginning of the first treatment session. Questionnaires assessing participants’ acceptance of both interventions are completed at post and follow-up. The sociodemographic interview and all other measures, including semi-structured interviews for schizophrenia symptoms (PANSS and PSYRATS), self-report questionnaires, and neuropsychological measures are completed at all three testing sessions (see Table 2 for list of measures and administration time points).

**Table 1 Tab1:** Schedule of enrollment, interventions, and assessments

	Study period				
	Enrollment	Randomization	Intervention (12 bi-weekly sessions)	Post (6 weeks)	Follow-up (6 months)
Timepoint	T-1	T0		T1	T2
Enrollment					
Eligibility screen	X				
Informed consent		X			
Randomization		X			
Interventions					
MCT+			X		
Cognitive Remediation			X		
Assessments					
Baseline		X			
Post-intervention				X	
Follow-up					X

**Table 2 Tab2:** List 1 of study measures and questionnaires

Instrument	Baseline	6 weeks (post)	6 months (follow-up)
*Diagnostic and Measures of Psychopathology*			
Sociodemographic interview	X	X	X
Mini Neuropsychiatric Interview	X		X
Positive and Negative Syndrome Scale	X	X	X
Psychotic Symptom Rating Scales	X	X	X
Calgary Depression Rating Scale	X	X	X
Personal and Social Performance Scale	X	X	X
Negative Symptom Assessment – 4	X	X	X
*Neurocognitive Measures*			
Trail Making Test A & B	X	X	X
Test d2	X	X	X
German Vocabulary Test (premorbid intelligence)	X		
Rivermead Behavioural Memory Test, Story Recall	X	X	X
*Cognitive biases*			
Fish Test	X	X	X
*Questionnaires*			
Short Form-12	X	X	X
Patient Health Questionnaire	X	X	X
Beck Cognitive Insight Scale	X	X	X
Rosenberg Self-Esteem Scale	X	X	X
Evaluation of the Intervention		X	X

A measure was developed by the authors (BS, FB, SM) to assess therapist adherence to the MCT+ manual. For patients who provide informed consent, therapy sessions are video recorded and psychologists familiar with MCT+ assess adherence. Additionally, questionnaires developed by the authors (SM) assessing participants’ acceptance of both interventions are completed after every training session attended.

Participants are allowed to use antipsychotic medications during the entire study and are not withheld from other psychosocial treatments they might be offered or are currently participating in, including participation in MCT group therapy. Participation in concurrent interventions is recorded at post- and follow-up testing sessions. Participants are allowed to withdraw from intervention or assessment sessions upon request without having to disclose a reason. All participants are compensated with 30€ upon completing of each assessment session.

### Randomization and assessor blindness

Treatment allocation is randomized via a computerized randomization plan (no stratification factors) and performed observer-blind. Extensive steps are taken to ensure rater blindness. The randomization plan is only accessible to the study coordinators, thus reducing the risk that assessors may be accidentally unblinded. Patients are informed that they are not to disclose their group assignment and are reminded of this at every testing session. At the end of the baseline testing session, all participants meet with a member of the research team who is not involved in testing and has access to the site-specific randomization list. This individual gives the participant an envelope in which intervention assignment is identified. Raters are not involved in the active intervention. Rater blinding is verified by asking the rater to guess the participant’s treatment allocation at the beginning of every testing session and indicating their certainty.

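### Randomisation is described as unstratified yet run from site-specific lists, and site is not among the named ANCOVA covariates: a modest loss of precision, not a threat to validity

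*Protocol article*

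**What the plan says.** All the statements on allocation stand in one paragraph of the protocol article, under Randomization and assessor blindness.

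- On the method: "Treatment allocation is randomized via a computerized randomization plan (no stratification factors) and performed observer-blind".
- On access: "The randomization plan is only accessible to the study coordinators". The reason given is to protect assessor blinding.
- On hand-over, after baseline testing has ended: each participant meets "a member of the research team who is not involved in testing and has access to the site-specific randomization list". Then: "This individual gives the participant an envelope in which intervention assignment is identified".

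The Participants section names four clinics, and the Sample size section plans 82 patients at each. The Statistical analyses section specifies ANCOVA models and names the covariates: the baseline value, antipsychotic dose as a percentage of maximum, and concurrent treatment. Site is not named.

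**The concern.** Two statements in the paragraph do not fit together. If each clinic works from its own list, site is a stratification factor in practice, whatever the label. A reader cannot tell whether there was one unstratified plan or four site lists, and the answer decides which analysis matches the design. The usual principle is to analyse by the groups within which patients were randomised. The Discussion itself expects centres to matter, since it adds centres to reduce allegiance effects. A covariate list without site therefore forgoes precision that the design may already have provided for.

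The paragraph also uses two names for the list holder, study coordinators and a member of the research team. Its stated reason for restricting access is to keep assessors blind. It does not say how the list holder relates to those who enrol patients.

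**Working it through.** **1. The plan's own sample size.** Inputs from the Sample size section: d = 0.35, two-sided alpha 0.05, power 80%, dropout 20%, 4 centres.

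- Normal approximation: n per arm = 2 × (1.960 + 0.842)² / 0.35² = 128.2, rounded up to 129. The t-test version gives 129.1, rounded up to 130, as stated.
- Dropout: 260 / 0.80 = 325. The next multiple of 4 is 328 = 4 × 82, as stated.

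The stated figures reproduce, and nothing below changes them.

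**2. Effect of leaving site out.** Let rho be the share of outcome variance that lies between sites. The documents give no value, so a range of 0.01 to 0.10 is assumed. Also assumed: arms balanced within each site, 130 evaluable per arm, and a normal approximation with total SD 1. The 3 degrees of freedom spent on site are ignored; with 260 patients they hardly matter.

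- Standard error reported without site: sqrt(2/130) = 0.1240.
- Actual standard error when arms are balanced within site: sqrt((1 − rho) × 2/130).
- Actual alpha without site: 2 × [1 − Φ(1.960 / sqrt(1 − rho))].
- Power without site: Φ((0.35 − 1.960 × 0.1240) / actual SE).
- Power with site: Φ(0.35 / actual SE − 1.960).

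Worked case, rho = 0.10: actual SE = 0.1240 × sqrt(0.90) = 0.1177. Alpha = 2 × [1 − Φ(2.066)] = 0.039. Power without site = Φ(0.1069 / 0.1177) = Φ(0.908) = 81.8%. Power with site = Φ(2.974 − 1.960) = Φ(1.014) = 84.5%.

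| Assumed rho | Actual alpha, site omitted | Power, site omitted | Power, site included | Loss (points) |
|---|---|---|---|---|
| 0 | 0.050 | 80.6% | 80.6% | 0 |
| 0.01 | 0.049 | 80.7% | 81.0% | 0.3 |
| 0.02 | 0.048 | 80.8% | 81.3% | 0.5 |
| 0.05 | 0.044 | 81.2% | 82.5% | 1.3 |
| 0.10 | 0.039 | 81.8% | 84.5% | 2.7 |

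The losses are taken from unrounded power.

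**3. The access statements side by side.** One sentence confines the plan to study coordinators, in the plural. The other gives list access to a team member who does no testing. Both are true if that member is the clinic's study coordinator. No section gives this person a recruiting or screening task: the section on procedure and treatment allocation assigns screening to research assistants, and the Intervention section assigns treatment to psychologists in post-graduate training. Equally, no section states that the list holder is kept out of recruitment and eligibility decisions.

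**The case against.** **Separate lists need not mean stratification.** A site's list could be that site's portion of one computerised plan, and the article mentions no blocking or balancing within site. With unrestricted randomisation there is no restriction for the analysis to match, and omitting site then leaves alpha at its nominal level. This stands, and it is why the figures above are conditional on balanced lists. It does not remove the need to say which design was used.

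**An analysis plan that is not shown may add site.** This is possible. The article nevertheless sets out its covariates without site, so the correction is worth making there too.

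**A reader might infer that omitting site endangers the type I error.** The calculation goes the other way: with balanced lists the test is slightly conservative.

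**A reader might infer that the access sentences contradict each other and that upcoming allocations could be exploited in recruiting.** The documents do not support this. A site coordinator satisfies both sentences. List access is stated only for the person who hands over the envelope, and that person has no stated part in choosing patients. Consent and baseline testing precede the hand-over. Details such as envelope type, numbering and block size are what an article commonly leaves to the full protocol. Any figure for selection bias would need inputs that the documents do not give, so none is offered. What remains is an ambiguity about roles.

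**Conclusion.** The concern holds in a limited form. The paragraph denies stratification while describing site-specific lists, and the named covariates omit site. If the lists are balanced within site and site explains 1 to 10% of outcome variance (an assumption), omitting site lowers actual alpha to about 0.049 to 0.039 and costs about 0.3 to 2.7 points of power. That is a small, conservative inefficiency with no inflation of type I error and no effect on the planned 328 patients. The wording on who holds the list is unclear and should be tightened, but it is not evidence that allocation concealment failed.

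**What to change.** - State whether allocation uses a separate list per site. If it does, replace the statement that there are no stratification factors with one naming site as the factor.
- Add site (4 levels, 3 degrees of freedom) as a fixed factor in the primary and secondary ANCOVAs.
- As a secondary clarification, name the single role that holds the list, and state that this person takes no part in recruitment or eligibility decisions.

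The cost is a few sentences and one model term; the sample size does not change. The Trial status section reports that recruitment was still under way at submission, so the model term can be fixed before outcomes are analysed.
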